## 4.6 Sub-group analyses

Subgroup analyses will be undertaken on the primary outcomes i.e., physical activity and mobility. All subgroups will be defined by data collected prior to randomisation. Subgroup analysis will be conducted on each of the primary outcomes for:

- Neurological versus non-neurological condition
- Sex (male versus female)
- Age (age entered as continuous covariate and as categorical (above and below median age); both analyses will be considered)
- Baseline mobility level (analysis with 12-point SPPB as a continuous interaction term with data also presented as a dichotomous term above and below median)
- Technology use prior to hospital admission (used vs. not used a computer, tablet, smartphone, pedometer or gaming console in the month prior to hospitalisation)
- State (NSW versus SA)

Unadjusted *p*-values will be reported and the number of declared subgroup analyses will be specified in all publications. The main analysis for each subgroup will be an interaction test in the linear regression model to determine whether the effect of treatment differs significantly across categories for that particular subgroup. The between-group differences within each of the subgroups will be reported, as well as the *p*-value for the interaction test.

## 4.7 Economic evaluation (this will not be reported as part of the main paper)

Health and community service usage data collected from participant-completed calendars, hospital databases and medical records (rehabilitation length of stay, readmissions including type, other settings length of stay e.g. transitional care, number and type of community services at home) will be used to calculate health service utilisation and costs to inform the conduct of an economic evaluation. The cost of the intervention (staff and equipment) will also be calculated from trial records and used in the cost effectiveness analysis. The Incremental Cost-Effectiveness Ratio will be calculated to assess the relative costs and benefits in terms of gain in mobility (the proportion of participants achieving a clinically meaningful improvement on the 12-point SPPB scale) and QALYs.

## 4.8 Exploratory analyses

A sensitivity analysis may be undertaken for the primary outcome ‘Upright time’ including all data regardless whether it meets the *apriori* valid weartime.

Further analyses may be undertaken to explore differential effects by the subgroups outlined above for the secondary outcomes.

Further exploration based on intervention adherence may also be conducted.

## 4.8 Intervention group measures

Adverse events reported in the intervention group, adherence, impression of ‘usability’ and ‘enjoyment’ will be summarised.

## Appendix 1: Primary and Secondary Outcome Measures

| *Outcome measures*  *PO: Primary Outcome* | *Time points* | | | *Variable Type* | *Scoring* | *Best outcome* | | | | *Value assignment for participants physically unable to perform tests* |
| --- | --- | --- | --- | --- | --- | --- | --- | --- | --- | --- |
|  | *3*  *wks* | *12 wks* | *6 mths* |  |  | *High* | *Low* | | |  |
| **Balance and mobility** | | | | | | | | | | |
| activPAL | ✓ |  | ✓ | Continuous | Upright time: time spent stepping and standing. | ✓ | |  | Assign 0 | |
| Short Physical Performance Battery (SPPB) - Lower extremity continuous summary performance score (CSPS)^1^ | ✓ |  | ✓ | Continuous | Score 0–3 | ✓ | |  | A value corresponding to the 99th percentile of baseline performance of participants completing the task was assigned to participants who were unable to perform the task or who had a performance below the 99^th^ percentile (walking speed: 11.2 cm/sec). A value corresponding to the 99th percentile of baseline performance of participants completing the task was assigned to participants who were unable to perform the task or who had a performance above the 99th percentile (chair stands: 83 s)  Balance tests: assign 0 | |
| Short Physical Performance Battery (SPPB) + individual components^2^ | ✓ |  | ✓ |  | Total score 0-12  Subscale scores 0-4 | ✓ | |  | Assign 0 for gait velocity standing balance and chair stand if physically unable to do it. | |
| De Morton Mobility Index^3^ | ✓ |  | ✓ | Continuous | Raw score out of 19  DEMMI score between 0-100 | ✓ | |  | Assign 0 | |
| Maximal balance range test^4^ | ✓ |  | ✓ | Continuous | Measured in mm | ✓ | |  | Assign 0 | |
| Step Test^5^ | ✓ |  | ✓ | Continuous | Step count, average of both legs | ✓ | |  | Assign 0  Average of 2 legs. | |
| Single Leg Stance | ✓ |  | ✓ | Continuous | Measured in seconds, up to 10 seconds | ✓ | |  | Assign 0 | |
| **Activity and participation** | | | | | | | | | | |
| WHO Disability Assessment Schedule 2.0^6^ | ✓ | ✓ | ✓ | Continuous | Raw score 12-60, |  | | ✓ | Missing data if not completed | |
| **Physical activity** | | | | | | | | | | |
| Incidental and Planned Exercise Questionnaire^7^ | ✓ | ✓ | ✓ | Continuous | Total score 0-182 | ✓ | |  | Missing data if not completed | |
| **Falls related confidence** | | | | | | | | | | |
| Activities-Specific Balance Confidence Scale^8^ | ✓ | ✓ | ✓ | Continuous | Total score 0-100 | ✓ | |  | Missing data if not completed | |
| **Cognition** | | | | | | | | | | |
| Trails A & B^9^ | ✓ |  | ✓ | Continuous | Difference in time between the two parts. | ✓ | |  | A: unable or score>2 min will be adjusted to 120 s  B: unable or score>5 min will be adjusted to 300 s | |
| **Health-related quality of life** | | | | | | | | | | |
| European Quality of Life-5 dimensions  (EQ-5D-5L)^11^ | ✓ | ✓ | ✓ | Continuous | Each of the 5 dimensions are scored 1-5, each of these scores are assigned a value from the scoring algorithm; and the VAS is scored 0-100 | ✓ | |  | Missing data if not completed (For economic analysis: missing data will be imputed by using the midpoint of previous and following values and carrying forward last observation) | |
| Short Form 6-dimensions questionnaire (SF-6D) calculated from the SF-36^12^ | ✓ | ✓ | ✓ | Continuous | Responses are tallied and converted into the SF-6D utility score determined from a published algorithm | ✓ | |  |  |  |
| **Technology self-efficacy** | | | | | | | | | | |
| Modified Computer Self-Efficacy Scale (MCSE)^13^ | ✓ | ✓ | ✓ |  | Scored 10-100 | ✓ | |  | Missing data if not completed | |
| **Falls** | | | | | | | | | | |
| Number of falls, adverse events, deaths | Monthly | | | Continuous |  |  | | ✓ | Missing data if not available | |
| **Health and community service usage** | | | | | | | | | | |
| Number of contacts with health and community services | Monthly | | | Continuous |  |  | | ✓ | Missing data if not available | |
| **Additional intervention group only measures** | | | | | | | | | | |
| System Usability Scale (SUS)^14,15^ | ✓ | ✓ | ✓ | Continuous | Scored 0-100 | ✓ | |  | Missing data if not completed | |
| Physical Activity Enjoyment Scale (PACES)^16^ | ✓ | ✓ | ✓ | Continuous | Scored 18-126 | ✓ | |  | Missing data if not completed | |

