**Activity and participation**, the WHO Disability Assessment Schedule 2.0 (WHODAS 2.0)^6^, a 12-item self-report measure of activity performance and participation covering 6 domains, will be completed at 3 weeks, 12 weeks and 6 months. The scores assigned to each of the 12 items – “none” (1), “mild” (2) “moderate” (3), “severe” (4) and “extreme” (5) – are summed to give a score ranging from 12 to 60, where 12 = no disability and 60 = full disability.

**Physical activity**, the 10-item Incidental and Planned Exercise Questionnaire^7^ assesses the level of physical activity relating to both basic and more demanding activities at 3 weeks, 12 weeks and 6 months. The total time spent doing activities is summed across all components and expressed as hours per week. The score is derived from multiplying frequency score and duration score (see Appendix 4) to create a total duration for the week score: Total activity score = (Q1*Q2) + (Q3*Q4) + (Q5*Q6) + (Q7*Q8) + (Q9*7) + (Q10*7), with a higher score indicating a higher physical activity level. Subscale scores will also be calculated for home exercise (Q2) and walking activity (Q5*Q6)+(Q6*Q7).

**Fall-related confidence** will be assessed with the Activities-Specific Balance Confidence Scale^8^ at 3 weeks, 12weeks and 6 months. This is a 16-item scale with each item scored between 0 to 100 with 0 representing no confidence and 100 representing complete confidence. The 16 items are summed together and then divided by 16 (the number of items) to give a total score between 0 and 100 with a higher score indicating a higher confidence in balance.

**Cognition**, will be assessed using the Trail Making Test parts A and B^9^ at 3 weeks and 6 months. Trails Part A measures processing speed and involves participants connecting consecutive numbers (e.g., 1-2-3). Part B is a measure of executive function of ‘task shifting’ and involves participants connecting alternating letters and numbers (e.g.,1-A-2-B). The difference in time between the two parts (B minus A) will be calculated to isolate the executive component of this test with a lower time reflecting better executive function.^10^ Trails Part A score and Trails Part B scores will also be calculated.

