## 4.2 Data quality and blind review

Data quality checks will initially be conducted in REDCap. Range checks will be performed for each variable at each time point. The following tasks will be conducted blinded to group allocation: 1) Missing and out of range data in REDCap will be checked against paper data collection forms to confirm values and corrected in REDCap; 2) activPAL data will be cleaned and corrected in REDCap as outlined in appendix 2; 3) replacement of missing data for participants unable to perform the test task as outlined in appendix 1.

Once this process is complete and continuing using a blinded review range checks will be performed for each variable at each time point and histograms will be visually inspected for each variable at each time point using stata. The distribution of continuous variables will be evaluated to inform whether change scores will be used for analysis.

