## 4.5 Secondary outcomes

Physical Activity:

- The effect of group allocation on the continuous variable time spent upright (minutes per day averaged over days worn), assessed using the activPAL activity monitor at 3 week follow-up will be analysed using linear regression models with baseline scores entered into the linear regression models as covariates.
- The effect of group allocation on the continuous variable ‘average number of steps per day’ assessed using the activPAL activity monitor at 3 weeks and 6 months follow-up will be analysed using linear regression models with baseline scores entered into the linear regression models as covariates.
- average number of transitions per day’ at 3 weeks and 6 months follow-up will be analysed using linear regression models with baseline scores entered into the linear regression models as covariates.

Mobility:

- For this continuous secondary outcome, the groups will be compared on 3 week assessment CSPS, adjusted for baseline scores.
- A secondary analyses will be conducted using the 12-point scored version of the Short Physical Performance Battery^2^ and the sub-scores for the three test items: standing time with the feet in different positions (together, side by side, semi-tandem, tandem and single leg stance) (0-4), 4-metre walk (0-4), and repeated chair stand test (0-4). For these outcomes, the groups will be compared at 3 weeks and 6 months, adjusted for baseline scores.

For the other continuous secondary outcomes (see Appendix 1), the effect of group allocation at the specified time points cognition (3 weeks and 6months after randomisation), self-reported physical activity, activity performance and participation; quality of life, balance confidence and technology self-efficacy (3 and 12 weeks and 6 months after randomisation) will be analysed using linear regression models with baseline scores entered into the linear regression models as covariates. Or if distributions are overly skewed (on visual inspection of histograms) the change scores (post-pre) will be analysed. Mean between-group differences and their 95% CIs will be reported. In addition, self-reported measures of technology usability and enjoyment will be obtained from the intervention group (3 and 12 weeks and 6 months after randomisation).

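### Once Trails B is capped at 300 s, the planned B minus A score becomes 300 minus A, so a slower Part A reads as better executive function

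*SAP*

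**What the plan says.** SAP section 3.2 (Cognition) defines the score: "The difference in time between the two parts (B minus A) will be calculated to isolate the executive component of this test". The direction is set as lower is better, and separate scores for the two parts are also planned: "Trails Part A score and Trails Part B scores will also be calculated".

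The Trails row of Appendix 1 gives the scoring as "Difference in time between the two parts". In the column for participants physically unable to perform the test it states "A: unable or score>2 min will be adjusted to 120 s" and, for the second part, "B: unable or score>5 min will be adjusted to 300 s". The same row ticks High as the best outcome, whereas section 3.2 describes the difference "with a lower time reflecting better executive function".

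Section 4.2 lists, among the blinded cleaning tasks that come before analysis, "replacement of missing data for participants unable to perform the test task as outlined in appendix 1". Under section 4.5 the cognition outcomes at 3 weeks and 6 months "will be analysed using linear regression models with baseline scores entered into the linear regression models as covariates", or change scores are used if the distributions are too skewed.

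The SAP has no separate rule for the difference when one or both parts are capped.

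**The concern.** Capping each part on its own is harmless, because the slowest performers all sit at the poor end of that part. Subtracting one capped part from another is different. When B is held at 300 s, only A can vary, and it enters with a minus sign. Among participants who fail B, those slowest on A get the lowest and so best-looking score.

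At stake is the interpretation of the executive-function outcome. A gain in processing speed among participants whose Part B stays capped would be recorded as executive decline. The same misordering is present in the baseline covariate, and it feeds directly into the change score if that fallback is used.

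**Working it through.** **Inputs from the SAP.** Cap on A 120 s and cap on B 300 s (Appendix 1); score B minus A, lower better (section 3.2); values assigned during data cleaning (section 4.2). The SAP states no figure for this score that could be reproduced. The individual times below are assumed for illustration.

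**Formula.** D = min(B, 300) − min(A, 120), with A = 120 if unable on A and B = 300 if unable on B. Whenever B is capped, D = 300 − min(A, 120). A participant unable on B has no time to subtract from, so D can only be formed from the assigned 300 s.

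**Ordering of individuals**

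| Part A | Part B | D |
|---|---|---|
| unable | unable | 300 − 120 = 180 s |
| 90 s | unable | 300 − 90 = 210 s |
| 60 s | unable | 300 − 60 = 240 s |
| 40 s | unable | 300 − 40 = 260 s |
| 40 s | 250 s | 250 − 40 = 210 s |
| 60 s | 280 s | 280 − 60 = 220 s |
| 60 s | 200 s | 200 − 60 = 140 s |
| 100 s | 250 s | 250 − 100 = 150 s |

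The lowest D available with B capped is 180 s, and it belongs to those also at the cap on A. Anyone with B capped and A under 120 s scores worse than someone unable on both. So does a completer of both parts whose difference exceeds 180 s. The last two rows show the limit: with both parts completed and a difference under 180 s, the order against those unable on both is right.

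**Change over time**

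- Unable on both, then A = 60 s with B still capped: 240 − 180 = 60 s, recorded as decline.
- Unable on both, then A = 50 s and B = 240 s: 190 − 180 = 10 s, recorded as decline although both tests were regained.
- A from 110 to 60 s and true B from 420 to 320 s: the uncapped difference falls from 310 to 260 s (better), while the capped score rises from 190 to 240 s (worse).

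**Group level, illustrative only.** Assumptions: lognormal times with standard deviation 0.5 on the log scale for both parts, correlation 0.7 between the log times, median B 2.5 times median A, and both parts made 10% faster. Over-limit times stand in for inability.

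| Assumed share over 300 s on B | Mean change, uncapped | Mean change, capped | Ratio | Mean change where B stayed at the cap |
|---|---|---|---|---|
| 10% | −10.7 s | −8.7 s | 0.81 | +5.0 s |
| 25% | −14.6 s | −8.9 s | 0.61 | +3.9 s |
| 40% | −18.0 s | −8.0 s | 0.44 | +3.0 s |

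The overall benefit shrinks but keeps its sign. The shrinkage includes what any ceiling on B would cause. The last column shows the wrong-direction component.

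**The case against.** **Subtracting A is the purpose of the score.** This holds while B is measured: a faster A with an unchanged B does mean a larger executive component. It does not hold at the cap, where B is a constant and the score says nothing about how slow B was.

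**The reversal is not general.** This stands. A reader might infer that the caps rank the most impaired ahead of the less impaired throughout. They do not: relative to participants unable on both, only those with B capped and A under 120 s, or with both parts completed and a difference above 180 s, are misplaced.

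**No impact on the trial result is shown.** This largely stands. The SAP gives no Part B completion rate, so a claim that many participants fail Part B is unsupported. A reader might also infer that the between-group effect would change sign; in the assumed scenarios it did not. The score is secondary and plays no part in the co-primary decision rule of section 4.1.

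**Parts A and B are scored separately.** True, and each capped part is ordered correctly. This limits the damage but leaves the difference, the score listed in Appendix 1, as it is.

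**The High tick.** It conflicts with section 3.2. Rows where low is best, such as WHODAS, are ticked in a different position, so table extraction is an unlikely cause. It is a labelling slip with no effect on the score or the model, and it adds nothing to the capping point.

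**Conclusion.** The rule is wrong as written, for one secondary outcome. Applied literally, the caps turn B minus A into 300 minus A for every participant with Part B capped, and that quantity runs against the stated direction of the score. This follows from the SAP's own figures and needs no assumption beyond reading section 4.2 as placing value assignment before the difference is taken.

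For an individual, the distortion reaches 60 s when A goes from unable to 60 s with B still capped. For the group comparison it cannot be sized from the SAP, because the share with B capped is not given. Under the assumed shares of 10% to 40%, the capped estimate kept 81% to 44% of the uncapped effect: attenuation, not reversal. The documents do not support a claim that the cognition conclusions as a whole, or the co-primary conclusions, are invalid.

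**What to change.** 1. In Appendix 1, state that when Part B is unable or over 300 s, B minus A is not computed as 300 minus A but set to one worst value. A workable choice is the 99th percentile of baseline B minus A among participants who completed A within 120 s and B within 300 s, with larger values truncated to it. This follows the device the SAP uses for gait and chair stands in section 3.1.
2. Report the number with Part B capped, by group and time point.
3. Interpret B minus A alongside the capped Part B time, which section 3.2 already plans.
4. As a separate correction, move the Trails best-outcome tick from High to Low, to agree with section 3.2.

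**Cost.** Wording and derivation code only, with no new data. There are two downsides. Participants will be tied at the worst value, and the score will jump at 300 s: with A = 110 s, B = 299 s scores 189 s, while B = 301 s takes the worst value (if that were 240 s, an assumption, a jump of 51 s for 2 s of performance). The change also leaves the cap on A in place when B is completed: true A = 150 s with B = 280 s still scores 280 − 120 = 160 s instead of 280 − 150 = 130 s.

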## Appendix 2: ActivPAL data cleaning

As this is our primary outcome and as we are aware that there were differences in how data was entered into REDCap (e.g. whether adjustments were done at the time of data entry), it was decided that all activPAL data should be checked and cleaned as part of the blind review process. Valid weartime was defined apriori as 4 days (24 hour periods).

Data to extract:

- Sit/Lie time (hours)
- Stand time (hours)
- Stepping time (hours)
- Number of steps
- Transitions (use 1^st^ value, number of ‘up’ transitions)
- Energy expenditure (MET.h)

The process for data cleaning was:

1. Open activPAL 3 software. Open the ‘View’ tab at the top and ensure that it is selected ‘View by week’ and “Analysis by 24 hour period. Using the file tab, select each participants activPAL file at 3weeks and 6 months. A one page file should open with graphs on it.
2. Check ‘Elapsed time’ at top of screen to confirm how many days the device collected data (should be 7 days).
3. Visually inspect the Summary by week bar graph (1^st^ graph) to determine if it looks as if device has been worn for total time data was collected. If it appears that the device was not worn of 1 or more 24 hour period (i.e. no steps or uptime recorded) view the detailed graph for that day to determine if the device was worn. If when looking at the summary graph it looks as if 1 or more 24 hour periods is considerably lower than the other days, again inspect the detailed graph of that day. If there is activity at different times through the day then it is likely they were wearing it but were inactive. If there was some activity for the first few hours and then nothing, then it is likely it fell off or was removed. In these scenarios only include the 24 hour periods when there was full data.
4. Below are some scenarios to describe what to do for each:
   1. Scenario 1: device data collection period 7x24 hours but device weartime 3x 24 hours (Figure). This data cannot be included in the analysis and should be removed with note in comments section in REDCap.
   2. Scenario 2: device data collection period 7x24 hours but device weartime just over 4 days (Figure b). Do not use summary values from Summary by week graph. Use sum of daily values for 4 valid 24 hour periods. Make note in comments section in REDCap.
   3. Scenario 3: device data collection period 4 days, 19 hours, 2 mins, 41 secs; weartime the same (Figure c). Do not use summary values from Summary by week graph. Use sum of daily values for 4 valid 24 hour periods. Make note in comments section in REDCap.
   4. Scenario 4: device data collection period 7x24 hours and weartime the same (Figure d). Use summary values from Summary by week graph.

**Figure a: 7 day data collection, 3 day valid weartime**

[figure not shown]

**Figure b: 7 day data collection, 4 day + 2hr valid weartime**

[figure not shown]

**Figure c: Data collection and weartime = 4 days 19 hours 2 minutes**

[figure not shown]

**Figure d: 7 day data collection, 7 day valid weartime**

[figure not shown]

Supplement: S3 Text — (DOCX) [file pmed.1003029.s011.docx]
